## Abstract

**Background:**

The COVID-19 pandemic has negatively impacted individuals with eating disorders; resulting in increased symptoms, as well as feelings of isolation and anxiety. To conform with social distancing requirements, outpatient eating disorder treatment in Canada is being delivered virtually, but a lack of direction surrounding this change creates challenges for practitioners, patients, and families. As a result, there is an urgent need to not only adapt evidence-based care, including family-based treatment (FBT), to virtual formats, but to study its implementation in eating disorder programs. We propose to study the initial adaptation and adoption of virtual family-based treatment (vFBT) with the ultimate goal of improving access to services for youth with eating disorders.

**Methods:**

We will use a multi-site case study with a mixed method pre/post design to examine the impact of our implementation approach across four pediatric eating disorder programs. We will develop implementation teams at each site (consisting of therapists, medical practitioners, and program administrators), provide a remote training workshop on vFBT, and offer ongoing consultation during the initial implementation phase. Therapists will submit videorecordings of their first four vFBT sessions. We propose to study our implementation approach by examining (1) whether the key components of standard FBT are maintained in virtual delivery measured by therapist self-report, (2) fidelity to our vFBT model measured by expert fidelity rating of submitted videorecordings of the first four sessions of vFBT, (3) team and patient/family experiences with vFBT assessed with qualitative interviews, and (4) patient outcomes measured by weight and binge/purge frequency reported by therapists.

**Discussion:**

To our knowledge, this is the first study to evaluate an implementation strategy for virtually delivered FBT for eating disorders. Challenges to date include confirming site participation and obtaining ethics approval at all locations. This research is imperative to inform the delivery of vFBT in the COVID-19 context. It also has implications for delivery in a post-pandemic era where virtual services may be preferable to patients and families living in remote locations, where access to specialized services is extremely limited.

**Trial registration:**

ClinicalTrials.gov NCT04678843, registered on December 21, 2020.

**Supplementary Information:**

The online version contains supplementary material available at 10.1186/s43058-021-00143-8.

## Background

### COVID-19, mental health, and eating disorders

The COVID-19 pandemic has had a tremendously negative impact on mental health, including heightened anxiety, depression, and psychological distress in populations all over the world [1–4]. Literature on the pandemic’s impact on individuals with eating disorders (EDs) and their families is slowly emerging [5–8]. During preliminary lockdown measures and relative to before the pandemic, individuals with EDs across Spain, the USA, Netherlands, Australia, and the UK reported exacerbations of ED symptoms and behaviors, higher concerns of relapse, and reduced motivation for recovery, while also expressing greater concerns about COVID-19 on their mental health than their physical health [6, 9–11]. Specifically among children and early adolescents, a children’s hospital in Perth, Australia, reported a substantial increase in the number of children with Anorexia Nervosa requiring admission to hospital for nutritional rehabilitation over the course of the pandemic [12].

Worldwide closures of day hospitals are leaving the most severely ill individuals with EDs without life-saving treatment [6]. Across Canada, most clinical settings are permitting only urgent outpatient visits for medical reasons or admission to inpatient units, and in-person mental health ambulatory visits are reduced or suspended in many areas. As the ED population is particularly vulnerable and at significant risk of medical complications and death should they not receive care [13], there is an urgent need to prioritize the implementation of effective virtual treatment options.

### Evidence-based treatment and their adaptation

The most widely used and supported evidence-based treatment for children with EDs (in particular Anorexia Nervosa) is family-based treatment (FBT) [14–16]. Despite a growing body of evidence supporting the clinical effectiveness of FBT adapted for virtual care [17–20], challenges remain in its implementation in our current context. A recent consensus panel discussion conducted as part of a Canadian Institutes of Health Research (CIHR)-funded COVID-19 Knowledge Synthesis project, aimed at developing virtual care clinical practice guidelines, revealed uncertainty about the strength of evidence for virtual care, and noted a number of challenges related to the virtual implementation of FBT [21]. These include the conduct of the family meal, supervision of mealtimes, reliance on caregivers for obtaining accurate weights, involvement of siblings in the treatment process, and unexpected termination of sessions. As the timeline of a return to in-person delivery of outpatient mental health services is unknown, it is anticipated that virtual care will be the primary method of treatment delivery for the foreseeable future [22]; it is also possible that a blended model of virtual and in-person ED treatment may be more common post-pandemic. While this may present opportunities by improving access to service, the nature of virtual treatment adaptations and their effective delivery requires examination to ensure patient outcomes do not suffer. Adaptations that focus on improving treatment fit with the target population can lead to improved engagement, acceptability, and clinical outcomes [23], but modifications that alter or remove core components of a treatment, or fail to align with population needs, may be less effective [24]. Failing to understand the type of modifications that occur and the systematic processes that lead to successful virtual treatment implementation within a given ED program may hinder outcomes [25, 26].

### Our previous implementation research

Our team recently completed research on the implementation of standard in-person FBT in Ontario within our pre-existing network of ED care providers [27–29]. We examined FBT implementation in four pediatric ED programs in Ontario [28]. Our implementation approach, informed by the Active Implementation Framework (AIF) [30], the Consolidated Framework for Implementation Research (CIFR) [31], and the Implementation Outcomes Taxonomy (IO) [32] included (1) the development of implementation teams at each site, (2) provision of FBT training, (3) monthly clinical and implementation consultation, and (4) fidelity assessment. Implementation effectiveness was assessed using mixed methods. We found that fidelity scores were similar to those in studies from academic centres [28]. Participants perceived our implementation approach as facilitating adoption of FBT in their organizations, and they were delivering standard FBT with fidelity to the key components of the model [28]. They reported that involving program administrators and medical practitioners (Doctor of Medicine [MD] or Nurse Practitioner [NP]) in implementation processes was essential to ensuring implementation success [27, 28]. Remaining highly engaged, the organizations requested ongoing consultation beyond the study time parameters [27–29].

### Study purpose and rationale

In light of the challenges caused by the COVID-19 pandemic and the evidence of clinical and implementation effectiveness of our approach [28], there is an urgent need and opportunity to adapt FBT for virtual delivery for adoption across our network. As noted above, the adaptations required for virtual delivery of FBT require examination to ensure maintenance of the key components and fidelity to the treatment. Therefore, we propose to study the initial implementation of virtual FBT (vFBT) in four pediatric programs in Ontario, with goals of building on our previous work, further developing clinical capacity for virtual care within our system, and improving access to evidence-based treatment for children with EDs in the COVID-19 context and beyond.

### Overview of our proposed research

We propose to study the initial adaptation and adoption of vFBT using the Quality Implementation Framework (QIF) [33] to guide our implementation process. The QIF provides a 14-step process to guide activities in four phases of implementation. This implementation process has been successfully applied in our own research in ED programs [28] and in research by team members with other child and youth mental health organizations [34]. The Implementation Outcomes Taxonomy (IO) [32] will guide evaluation of implementation outcomes. The Standards for Reporting Framework for Implementation Studies [35] (STaRI; co-authored by MB) will guide our methodology and reporting (see Additional file 1). The Standard Protocol Items: Recommendations for Interventional Trials (SPIRIT) checklist [36] will guide the evaluation of our study design (see Additional file 2).

### Research questions

Does our adaptation to vFBT maintain the key components of standard FBT by therapist self-report?Does our implementation approach for vFBT lead to implementation success at the participating sites, as measured by expert rating of fidelity to the vFBT model?What is the experience of implementation teams and patients/families implementing vFBT (and for therapists, does the experience change over time)?Do patients in vFBT demonstrate clinical outcomes similar to patients receiving standard FBT?

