### Study design

We will use a multi-site case study with a mixed method pre/post design [37] to examine our implementation approach. We will collect quantitative measures evaluating therapist adherence to key components of FBT, therapist fidelity to the vFBT model, therapist change in readiness, attitudes, and confidence in implementing vFBT over time, and patient outcomes (changes in weight and binge/purge frequency). Qualitative data will be collected using virtual focus groups and interviews to understand implementation team and patient/family experiences of vFBT.

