### Eligibility criteria

#### Therapists, medical practitioners, and program administrators

To participate in this study, these individuals must work in Ontario, Canada, have the ability to read, understand, speak, and write in the English language and have access to a working computer/electronic device with a stable internet connection. Specifically, therapists must have prior training and supervision in standard FBT and be actively delivering FBT within their treatment programs. Medical practitioners must either be doctors (MD) or nurse practitioners (NP). Program administrators must currently manage an ED program.

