### Procedures and timelines

#### Completed previously: phase 1—initial considerations regarding the host setting

Our implementation approach will follow the stages identified by the QIF [33]. Phase 1 site engagement and buy-in has been completed, by virtue of a well-established network that worked together on previous implementation studies. Of the four ED programs that voiced interest and capacity in implementing vFBT, two programs participated in our prior implementation study. The other two sites have subsequently received training in standard FBT through OCOPED training events. Also, during this time (pre-funding), we identified (with vFBT model co-developer JL) the types of adaptations required for virtual delivery in vFBT to ensure they do retain the key components of the standard FBT model, as these are essential for treatment effectiveness. These adaptations are summarized with the Framework for Reporting Adaptations and Modifications – Enhanced (FRAME) [38] in mind in Table 1.

**Table 1 Tab1:** Adaptations to family-based treatment (FBT) for virtual delivery

Component of FBT	What is the adaptation?	Why was the adaptation made?	Was the adaptation planned or unplanned?	What are the implications for fidelity?
**Weighing**	Therapist weighs patient virtually with patient at home instead of in clinic (home scale is required).	Patient is unable to come into the clinic for in-person visits.	Planned (proactive adaptation).	The patient’s weight is captured as intended. The process of weighing is maintained.
**Time spent alone with adolescent**	Parents are asked to leave the room for the first 10 min of the session so that individual time can be spent between the adolescent and therapist.	In a clinic setting, the adolescent is taken from the waiting room. In virtual therapy, family members often come on screen together, so parents must be asked gently and respectfully to leave.	Planned (proactive adaptation).	Time spent alone with adolescent is maintained.

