## Discussion

As outlined in this protocol, this implementation study will evaluate the processes involved in adapting and adopting vFBT to treat children and adolescents (<18 years) with Anorexia Nervosa. To examine the impact of our implementation approach, we will be using a multi-site case study with a mixed method pre/post design involving four Ontario-based pediatric ED programs. Site implementation teams have been established and consist of therapists, medical practitioners, and program administrators, who will all participate in a remote vFBT training workshop and receive ongoing support and consultation for the duration of the trial. Qualitative and quantitative measures will be used to measure: (1) vFBT maintenance of the key components of standard FBT by therapist self-report, (2) fidelity to the vFBT model by expert rating, (3) participant experiences with vFBT, and (4) patient outcomes. Using the findings of this pilot study, our long-term goal is to expand access to vFBT for all treatment-seeking children and adolescents with Anorexia Nervosa and other EDs.

The results of this study can be used to inform future implementation of vFBT across Ontario and even throughout Canada. The effectiveness of our implementation approach will provide validation of the QIF framework generally and within the context of guiding implementation of vFBT in other ED programs. Adaptations from standard FBT to vFBT and demonstrating fidelity to key components in this mode of delivery will further our understanding of the fundamental mechanisms required to effectively deliver virtual care in this field. Provision of training and supervision in vFBT will increase the capacity of therapists to deliver FBT virtually within Ontario’s ED network—so crucial as a viable option for outpatient care during the social distancing requirements brought on by the COVID-19 pandemic [48].

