The increased burden on healthcare services and associated clinical teams during COVID-19 [50] has already impacted our study preparations. Initially, we proposed to study six sites; however, two sites declined to participate due to higher-than-normal clinical caseloads and decreased staffing resulting from the COVID-19 pandemic. We have been unable to recruit replacement sites despite approaching seven other ED programs across Ontario.

We anticipate additional pandemic-related challenges during this study, but novel benefits of virtual care could also be revealed. Increased caregiver burden has been reported during telehealth visits, with accounts of parents having to weigh their child at home [8, 17], as well as additional burdens of supporting virtual school at home. However, increased time spent at home during COVID-19 has had positive effects on some families with EDs, such as building greater connections with family members and more time for self-care [9]. The second treatment session in FBT involves a family meal, with the therapist present and observing the family. While this is feasible during in-person treatment, therapists and families may find this challenging to complete virtually. However, there could be additional benefits to the family being within their own home during the observed family meal. This may present an opportunity to increase an insufficient meal due to the family being at home and able to supplement with food they already have. Technological challenges may reveal caregiver, patient, and/or therapist preferences for in-person rather than virtual treatment, although advantages to virtual care may also emerge, such as improved access to care for those located in remote areas, or greater convenience for families (i.e., no parking fees, no travel time, reduced need/cost for childcare).

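### Research question 2 and the QIF validation claim ask for an effect of the implementation approach, but fidelity is rated only after training and without a comparator, so the design can only describe it

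*Protocol article*

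**What the plan says.** Research question 2 reads: "Does our implementation approach for vFBT lead to implementation success at the participating sites", and names expert-rated fidelity to the virtual model as the measure of that success. Study design states: "We will use a multi-site case study with a mixed method pre/post design [37] to examine our implementation approach". The Abstract (Methods) and the opening paragraph of the Discussion both say that this design serves to examine the *impact* of the approach. The Discussion then draws the wider conclusion: "The effectiveness of our implementation approach will provide validation of the QIF framework generally".

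The timing and analysis of fidelity are fixed elsewhere in the article:

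- **Training:** the half-day workshop belongs to phase 2, months 0–4 (Procedures and timelines).
- **Rating:** each therapist records virtual sessions 1 to 4 with one family in phase 3, months 5–8. Experts rate these recordings on the FBT fidelity scale (Procedures and timelines; Measures, question 2).
- **Analysis:** the result is the percentage of therapists whose average score is at least 4 out of 7 on each session (Analysis, question 2). No change score or comparator is named.

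On who takes part, the eligibility criteria say that "therapists must have prior training and supervision in standard FBT and be actively delivering FBT within their treatment programs". Phase 1 says that "two programs participated in our prior implementation study" and that the other two sites have since been trained in standard FBT. Of the earlier study's participants, the Background reports that "they were delivering standard FBT with fidelity to the key components of the model". Under Setting, the four sites are described as programs that said they were interested, ready and able, out of a possible 22.

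**The concern.** To say that an approach leads to fidelity, one needs some view of what fidelity would have been without it, from an earlier rating or a comparison group. The plan has neither for this endpoint. It also enrols therapists who already practise the parent treatment and rates them on that treatment's own fidelity scale, so existing skill is an obvious competing explanation for a good result.

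What is at stake is the conclusion, not the data. If the plan is followed exactly and most therapists reach the threshold, the article's wording leads the reader to credit the approach and to treat the QIF as validated in general. The same result could arise if the approach contributed little. The article also calls itself a feasibility study (Sample size) and a pilot (Discussion), and a claim of general validation does not fit those labels.

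**Working it through.** **1. What each measure can show.** Setting the Measures and Analysis sections side by side:

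| Measure | Value before training? | Comparison group? |
|---|---|---|
| Key components, self-report (question 1) | No, once after session 4 | No |
| Expert-rated fidelity (question 2) | No, virtual sessions 1–4 only | No |
| Readiness, attitudes, confidence (question 3) | Yes, at consent, after the workshop and after session 4 | No |
| Weight, binge/purge frequency (question 4) | Baseline before treatment, not before training | 2 kg benchmark only |

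The pre/post label is accurate for questions 3 and 4. It does not extend to fidelity, which carries question 2.

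**2. Sample size reproduced.** 4 programs × 2 therapists on average = 8 therapists, as stated. With four sessions each, 8 × 4 = 32 recordings. No alpha, power or effect size is given, so there is nothing further to reproduce.

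**3. Precision of the descriptive answer.** Exact (Clopper–Pearson) 95% intervals for x of 8 therapists reaching fidelity. For 8 of 8 the lower limit is 0.025^(1/8) = 0.631.

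| Result | Exact 95% interval |
|---|---|
| 8/8 | 63% to 100% |
| 7/8 | 47% to 99.7% |
| 6/8 | 35% to 97% |

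**4. Could a high percentage arise with no effect of the approach?** Let p be the chance that such a therapist would reach the threshold in virtual delivery anyway. The documents give no value for p, so the range below is an assumption. P(at least 6 of 8) = Σ C(8,k) p^k (1−p)^(8−k) for k = 6 to 8, and P(8 of 8) = p^8.

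| Assumed p | P(at least 6/8) | P(8/8) |
|---|---|---|
| 0.50 | 0.145 | 0.004 |
| 0.60 | 0.315 | 0.017 |
| 0.70 | 0.55 | 0.06 |
| 0.80 | 0.80 | 0.17 |
| 0.90 | 0.96 | 0.43 |
| 0.95 | 0.99 | 0.66 |

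How a high percentage should be read depends on p, which the study does not estimate.

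**5. Would a pre-training rating rescue the causal claim?** With 8 pairs, a two-sided exact McNemar test needs at least 6 therapists changing, all in one direction: 2 × 0.5^6 = 0.031, whereas 2 × 0.5^5 = 0.0625. Under assumed changes with no reversals, the chance of this is 0.55 (20% to 90%), 0.14 (40% to 90%) or 0.01 (60% to 90%). A baseline would help to describe change. With eight therapists and no concurrent comparator, it would still not validate the QIF.

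**The case against.** The best defence is that question 2 is already descriptive in practice. It is confined to the participating sites, its measure is named, the analysis is a simple percentage and no hypothesis test is planned. A feasibility study needs no control group. A pre-training rating would concern FBT before the virtual model had been taught, which is a different quantity. Much of this stands: the endpoint, threshold and main analysis can stay, and no baseline need be demanded. It does not cover the statements about impact and general validation, which go beyond the descriptive reading. Because the article itself fixes when and how fidelity is measured, this is not detail left to a fuller document.

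A reader might also infer four stronger things that the documents do not support:

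- **That high scores are to be expected anyway.** No baseline fidelity in virtual delivery is given, and the earlier result concerned standard in-person FBT. The Background and Discussion describe specific virtual difficulties, such as the family meal and weighing at home. Carry-over is plausible but not shown.
- **That comparing returning with new sites would reveal carry-over.** Every therapist must be FBT-trained, so both groups have prior exposure. Each would have about four therapists if the average of two per program applies, and 4 of 4 has an exact interval of 40% to 100% (0.025^(1/4) = 0.40). Programs, not necessarily the same therapists, took part before.
- **That site uptake was 4 of 13 (31%).** This adds the six sites first proposed to the seven behind "We have been unable to recruit replacement sites despite approaching seven other ED programs across Ontario". The article does not give that sum, and the only denominator it states is 22. It does not say how many of the 22 were canvassed, so neither ratio is a measured uptake rate. The article openly reports the refusals.
- **That the pre/post label is wrong.** It holds for the measures under questions 3 and 4.

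**Conclusion.** The point holds as a mismatch between the question and conclusion on one side and the design on the other. The study can estimate the proportion of FBT-trained therapists who reach the fidelity threshold in virtual delivery under this approach, at four self-selected sites. The estimate will be imprecise: the best possible result, 8 of 8, leaves anything from 63% upward compatible with the data. The study cannot say how much of that fidelity the approach produced, and it cannot validate the QIF, in general or otherwise.

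This rests on the stated timing, eligibility criteria and analysis, and on about eight therapists. The direction and size of any carry-over are unknown; the probabilities under assumed values of p only illustrate why the percentage alone cannot settle the matter. Data collection is unaffected, but what the trial may conclude is.

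**What to change.** 1. Reword research question 2 along these lines: what proportion of FBT-trained therapists average at least 4 out of 7 on each of virtual sessions 1 to 4 under this implementation approach? Report the proportion with an exact 95% interval.
2. In the Discussion, drop the claim of general QIF validation and limit the statement to the feasibility of QIF-guided virtual FBT implementation at these sites. Bring the impact wording in the Abstract and in the opening of the Discussion into line.
3. State as a limitation that fidelity has no pre-training rating or comparator, and that earlier FBT training and site self-selection may contribute to the result.
4. Optionally, list fidelity results by prior-study and new site, as description only, with a note that this cannot isolate carry-over.

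The cost is a few sentences and one interval. No measure, threshold or data collection changes. The downside is a weaker headline claim.
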